### Eligibility criteria {10}

Participants meeting the following criteria will be included: Adult patients undergoing elective surgery involving general anesthesia with intubation, having an *American Society of Anesthesiologists* (ASA) score of I to III, who have given their consent according to the methods described in article L1122-1-1 of the French Public Health Code, and affiliated to a social security scheme or benefiting from such a scheme.

Participants meeting one or more of the following criteria will be excluded: age under 18 years, elderly patients aged over 75 years [21], general anesthesia without intubation (laryngeal mask), intraoperative local anesthesia with neuraxial block (peridural or spinal block), opioid-free anesthesia, arrhythmia or presence of a pacemaker, outpatient surgery, cardiac or cerebral surgery, obstetric surgery (Cesarean section), surgery performed with local neuraxial or peripheral anesthesia alone, surgery performed in prone position, emergency surgery, endoscopic procedure or interventional radiology, chronic pain treated by opioids, surgery scheduled to take less than 1 h, autonomous nervous system disorder (epilepsy, history of transient ischemic attack or stroke, paraplegia, hemiplegia, orthostatic hypotension, dysautonomia), patient suffering from cardiogenic or septic shock, continuous perfusion of vasoactive agents (ephedrine, phenylephrine, adrenaline or noradrenaline), scheduled postoperative transfer to ICU (patient intubated) after surgery, person under guardianship or curatorship, pregnancy, and breastfeeding.

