#### Relevant concomitant care permitted or prohibited during the trial {11d}

Authorized medicinal products are those normally used during general anesthesia. The patient’s routine treatments (antiplatelet drugs, β-blockers, and other antihypertensives, statins, etc.) will be managed in accordance with the current recommendations and the principles of good clinical practice. The following drugs are authorized within the scope of this trial: local anesthetics (levobupivacaine and ropivacaine), analgesics (ketoprofen, nefopam, paracetamol, tramadol), antiemetics (dexamethasone, droperidol, ondansetron), neuromuscular blocking agents (cisatracurium, succinylcholine), narcotics (desflurane, ketamine, propofol), and opioids (morphine, remifentanil).

The ANI calculation can be changed over 5 to 10 min following the administration of drugs affecting sinus cardiac activity (atropine, ephedrine, and phenylephrine mainly in the surgical context). If one or more of these drugs must be administered in the form of a bolus, this will be entered in the electronic case report form (eCRF), and the remifentanil dose will be maintained for the next 10 min without considering variations in ANI.

The continuous administration of vasopressors (ephedrine, phenylephrine, or noradrenaline) is prohibited during the study. If one or more of these drugs must be administered in the form of a bolus, this will exclude the patient from the study.

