### Assignment of interventions: allocation

#### Sequence generation {16a}

Randomization will be performed over the REDCap^®^ website (https://redcap.chu-clermontferrand.fr) to allow immediate allocation. The randomization list is balanced by blocks of variable and undisclosed size and stratified per center and per type of surgery. Patients will be randomized at day 0, after written informed consent is obtained and just before surgery. Each patient will be given a unique patient number and a unique randomization number. It is not possible to change group after randomization.

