## Statistical methods

### Statistical methods for primary and secondary outcomes {20a}

The main analysis will take the form of an intent-to-treat procedure using the Stata^®^ (version 13, StataCorp, College Station) and R (http://cran.r-project.org/) software; all of the statistical tests will be carried out with an α value of 5%. The continuous variables will be presented as mean and standard deviation, provided that distribution is normal (Shapiro-Wilk test, if required). In the event of an anomaly, they will be presented as median, quartiles, and ranges. Qualitative variables will be expressed in numbers and related percentages. Where feasible, graphs will accompany these analyses. Intergroup comparisons will be routinely carried out (1) without adjustment (2) by adjusting factors, the distribution of which might not be balanced between the groups, despite randomization.

The patients will be described and compared between the groups at baseline, according to the following variables: compliance with eligibility criteria, epidemiological characteristics, clinical characteristics, and possible treatments. The initial comparability of both arms will be assessed on the basis of the principal characteristics of participants and potential factors linked to the primary endpoint. Any difference between the two groups in terms of one of these characteristics will be determined based on clinical as opposed to purely statistical considerations. Protocol deviations, patients distributed according to these deviations, and reasons for withdrawal will also be described. The number of patients enrolled and the enrolment graph will be presented per group.

Since a 50% reduction in the incidence of immediate postoperative pain in PACU patients receiving ANI-directed intraoperative analgesia ranging from 50 to 80 must be highlighted, the primary endpoint (percentage of patients with NRS > 3) will be compared using the *x*^2^ paired test or Fisher’s exact test, if applicable.

Secondly, this analysis can be completed in a multivariate situation using a generalized, linear mixed model approach to logistics, considering inter- and intra-site variability. The covariables will be considered in terms of clinical relevance (other treatments, continuous use of vasopressors, type of surgery) and the results of previous univariate analyses. The results will be expressed in terms of related odds ratios and 95% confidence intervals.

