For the other qualitative parameters (percentage of patients with a NRS > 3 on the first day following surgery, postoperative complications on the first and seventh days after surgery, and patient destination following surgery (surgery unit, continuous care, intensive care), analyses relating to the secondary objectives will focus on the same approach as that previously recommended for the primary endpoint.

The quantitative secondary endpoints (maximum pain score on the first day following surgery, PACU dose levels of morphine, total dose of morphine on the first day following surgery, duration of PACU (time taken to obtain an Aldrete score ≥ 9), duration of hospital stay) will be compared between the groups using Student’s *t* test or Mann-Whitney’s non-parametric test if the *t* test conditions are not respected (normality study, homoscedasticity studied using the Fisher-Snedecor test). The results will be expressed in terms of effect size and 95% confidence interval. These analyses can be completed a second time in a multivariate situation using linear regression models. The covariables will be considered in terms of clinical relevance and the results of previous univariate analyses. The results will be expressed in terms of related regression coefficients and 95% confidence intervals.

Survival on day 28 post-surgery will be estimated according to the Kaplan-Meier curve and compared between the randomization groups using the log-rank test in a univariate situation and Cox’s model in multivariate analysis. The results will be expressed in terms of the immediate relative risk ratio and 95% confidence intervals.

Part of the analyses concerning the secondary endpoints will be exploratory in nature and should lack statistical power. As discussed by Feise in 2002, adjustment of the *p* value will not be proposed routinely but on a case-by-case basis depending on clinical as opposed to purely statistical considerations [25].

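### The supplementary adjusted model names continuous vasopressor use, which can only be constant or post-randomisation, as a covariate and lets trial data choose others, so its odds ratio can be biased and is not fixed in advance

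*Protocol article*

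**What the plan says.** All places are in the protocol article.

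- **Primary test.** Section {20a} states that "the primary endpoint (percentage of patients with NRS > 3) will be compared using the" chi-square or Fisher's exact test, by intention to treat and without covariates.
- **Adjusted model.** The same section continues: "Secondly, this analysis can be completed in a multivariate situation using a generalized, linear mixed model approach to logistics". Its covariates are to be considered for "clinical relevance (other treatments, continuous use of vasopressors, type of surgery) and the results of previous univariate analyses". Odds ratios with 95% confidence intervals are announced directly after this model.
- **Adjustment in general.** Between-group comparisons are to be made routinely without adjustment and then "by adjusting factors, the distribution of which might not be balanced between the groups, despite randomization".
- **Other endpoints.** The secondary qualitative endpoints (day-1 NRS > 3, complications, destination after surgery) follow the approach of the primary endpoint. For the linear models of the quantitative endpoints: "The covariables will be considered in terms of clinical relevance and the results of previous univariate analyses".
- **Vasopressors elsewhere.** Eligibility criteria {10} exclude patients with "continuous perfusion of vasoactive agents (ephedrine, phenylephrine, adrenaline or noradrenaline"). Section {11d} says: "The continuous administration of vasopressors (ephedrine, phenylephrine, or noradrenaline) is prohibited during the study". Sample size {14} nevertheless lists continuous vasopressor use among the reasons for enrolling 380 patients instead of 322.
- **Timing.** Sequence generation {16a}: "Patients will be randomized at day 0, after written informed consent is obtained and just before surgery". Randomisation is stratified by centre and type of surgery.

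**The concern.** Covariates in a randomised comparison should be fixed before randomisation or incapable of being altered by it. A variable that arises later and responds to the assigned arm causes two problems. If it lies on the path from treatment to outcome, adjusting for it removes part of the effect. If it shares unmeasured causes with the outcome, adjusting for it induces an association between arm and those causes, and can create an apparent effect where none exists.

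Continuous vasopressor use is open to this. The intervention titrates remifentanil ({11a}), the background {6a} links high remifentanil doses to hypotension, and better intraoperative haemodynamics is a stated secondary objective ({7}). Infusion use could plausibly differ by arm.

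The second issue is selection. Choosing covariates from univariate results, or from imbalances seen in the data, means that the model is known only after the data have been examined. Several adjusted answers are then available.

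At stake is the adjusted odds ratio. It matters because {20a} names no other effect measure with a confidence interval for the primary endpoint; none is stated with the chi-square or Fisher test.

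**Working it through.** **1. The plan's own sample size.** Inputs from {14}: control incidence 30%, a 50% reduction (to 15%), two-sided 5%, power 90%.

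n per group = [z(0.975)·√(2·p̄·(1−p̄)) + z(0.90)·√(p₁(1−p₁)+p₂(1−p₂))]² / (p₁−p₂)²

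With p̄ = 0.225: [1.960·√0.34875 + 1.2816·√0.3375]² / 0.15² = [1.1575 + 0.7445]² / 0.0225 = 160.8, so **161 per group**. The stated figure is reproduced.

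Power at n per group = Φ{[0.15·√n − 1.1575] / 0.5809}. This gives 90.0% at 161 and 94.1% at 190. Neither figure involves a covariate, so the sample size and the power of the unadjusted test do not depend on this point.

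**2. When can continuous vasopressor use occur?**

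| Section | Statement on continuous vasopressors | Consequence |
|---|---|---|
| {10} | Exclusion criterion | Not present at entry |
| {16a} | Randomisation just before surgery | An infusion started in theatre comes after randomisation |
| {11d} | Prohibited during the study | If fully observed, the covariate is zero for everyone |
| {14} | Anticipated; one reason for the larger enrolment | Expected to occur in some patients |
| {20a} | Named as a covariate | Expected to vary among analysed patients |

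Two cases remain. If the prohibition holds, the covariate is constant and contributes nothing. If it does not, the covariate is an event after randomisation. In neither case is it a baseline characteristic.

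**3. Direction.** Suppose arm changes the chance of an infusion, and an unmeasured feature (for example, intensity of surgical stimulation) affects both infusion and pain. Within infused or non-infused patients the arms then differ in that feature although randomisation balanced it. The sign of the resulting bias depends on whether the intervention raises or lowers infusion use, and on whether the shared feature moves infusion and pain the same way or in opposite ways. The document settles neither, so the bias cannot be assumed conservative.

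**4. Size.** It depends on how often infusions occur, how strongly arm changes that frequency, and how strongly infusion is related to pain. None of the three is given. The only related figure is the enrolment allowance: 380 − 322 = 58, and 58/380 = 15.3%. That allowance also covers direct transfer to ICU or continuous monitoring, so the planned infusion frequency on its own should be lower. It is a planning figure, not an observed limit.

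**5. Other covariates named or implied.**

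- Type of surgery is a stratification factor known at randomisation, and is unobjectionable.
- Other treatments are not defined in time. Routine medication such as β-blockers ({11d}) would be baseline; intraoperative analgesics, also listed in {11d}, would not.
- Univariate results are a data-dependent route for both the logistic and the linear models. Observed imbalance is a second such route, stated for comparisons in general.

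**The case against.** The strongest reply is about status. The main analysis is unadjusted, the model comes second and is worded as something that can be done, and covariates are only to be considered. **This stands**: the trial's primary conclusion does not rest on the model. It does not dispose of the point, because the same section makes adjusted comparisons routine and attaches the odds ratio and interval to this model.

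A second reply is that covariate lists belong in the analysis plan, which is not shown. That would answer silence. Here the protocol names an unsuitable covariate and states the selection routes.

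A third reply is that {20a} judges baseline differences clinically and not purely statistically. That moderates the imbalance route but still chooses the model after the data are seen.

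A reader might infer more than the document supports:

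- **That other treatments means analgesics given during or after surgery, including rescue in PACU.** {20a} does not say so. The paragraph on baseline comparison mentions possible treatments, so a baseline reading is equally open. PACU morphine dose is listed as a secondary outcome, and PACU rescue is not named as a covariate. The fault is that the term is left open.
- **That the bias is large.** Continuous infusion is prohibited, and the combined allowance is about 15%.
- **That a random site effect with three centres is an error.** The model does account for centre; fixed or random is a modelling preference.
- **That the Cox model has the same fault.** {20a} names no covariates for it.

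**Conclusion.** The point holds for the supplementary logistic model of the primary endpoint and for the secondary qualitative endpoints that follow the same approach. Continuous vasopressor use is either a constant or a post-randomisation event that the intervention may affect, and adjusting for it **can** bias the odds ratio in either direction. The stronger statement, that the adjusted estimate will be biased, is not supported: it would require infusions to occur and to be affected by arm, and the document shows neither.

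The size is not derivable and is probably modest if infusions are uncommon. The unadjusted primary test, the 161 per group and the 190 per group are unaffected.

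Separately, and without any assumption about vasopressors, selecting covariates by univariate results or observed imbalance makes the adjusted estimates data-dependent. The univariate route applies to the linear models too. This is worth correcting, but it does not threaten the primary test.

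**What to change.** 1. Delete continuous use of vasopressors from the covariates in {20a}.
2. Restrict other treatments to named treatments recorded before randomisation.
3. Replace univariate and imbalance-driven selection, in the logistic and the linear models, with one pre-specified model: arm, centre, type of surgery (the stratification factors) and a short named list of baseline covariates.
4. Report vasopressor and co-analgesic use by arm descriptively.
5. Reconcile {10}, {11d}, {14} and {20a} on continuous vasopressors. They currently exclude, prohibit, anticipate and adjust for the same event. Which clinical rule should apply is for the sponsor.

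The cost is wording in the statistical section, with no change to the sample size or the primary test. Centre and type of surgery are known at randomisation. The article lists no eCRF variables, so the sponsor should confirm that any further baseline covariate is recorded. The change is most credible if made before outcome data by arm are seen.

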### Interim analyses {21b}

An interim analysis will be scheduled halfway through the enrollment period (95 patients per group).

### Methods for additional analyses (e.g., subgroup analyses) {20b}

Additional analyses are not planned.

### Methods in analysis to handle protocol non-adherence and any statistical methods to handle missing data {20c}

Data will be analyzed using an intention-to-treat methodology. A sensitivity analysis will be proposed to define the attrition level and statistical nature of the missing data in order to propose the most appropriate imputation method (maximum bias or multiple imputation), if applicable.

### Plans to give access to the full protocol, participant-level data, and statistical code {31c}

The full protocol, participant-level dataset, and statistical code will be available in accordance with Clermont-Ferrand University data sharing protocols.

### Oversight and monitoring

#### Composition of the coordinating center and trial steering committee {5d}

The trial steering committee is composed of investigators from the departments of anesthesiology and intensive care. The chair of the steering committee, through the Clermont-Ferrand University Hospital Centre, will be coordinating this study.

#### Composition of the data monitoring committee, its role, and reporting structure {21a}

The research assistant of Clermont-Ferrand University Hospital Centre will be coordinating the data monitoring committee. Serious adverse events will be reviewed regularly by the study steering committee and reported to the ethics committee.

#### Adverse event reporting and harms {22}

Adverse events will be collected in accordance with the Ethics Committee guidelines. Serious adverse reactions will be reported to the institutional research support services at each site. Significant safety issues will be reported to the Ethics Committee.

#### Frequency and plans for auditing trial conduct {23}

After each site is activated and has enrolled at least five patients, site monitoring of the consenting process, protocol adherence, and data collection will be conducted. At the end of this study, all sites will be monitored for protocol adherence and completion of data collection.

#### Plans for communicating important protocol amendments to relevant parties (e.g. trial participants, ethical committees) {25}

Any amendments to the protocol must be qualified as substantial or non-substantial. If they are deemed to be substantial, they must be reviewed by the ethics committee. Furthermore, any extension to the trial (in-depth amendment to the treatment design or cohort enrolled, prolonged administration of treatment, and/or therapeutic procedures not initially provided for in the protocol) must be classed as a new trial. Any deviations from the protocol will be fully documented using a breach report form.

#### Dissemination plans {31a}

The study shall be the subject of a declaration before being included on the internet site and made accessible to the general public [ClinicalTrials.gov]. The sponsor owns the data and this information cannot be used by or transmitted to a third party without the sponsor’s prior consent. The names of the sponsor, all of the investigators involved in patient recruitment or follow-up, methodologists, biostatisticians, and data managers participating in the trial will be mentioned when the main results are published. International regulations governing writing and publication shall be taken into account [26]. For the main publication, the scientific coordinator will be mentioned as the first author and the coordinating investigator as the last author.

## Discussion

The GOALDAN study has been designed to be pragmatic. Although anesthesia protocol is well codified in the experimental group, it remains however highly permissive concerning dose of anesthetics, analgesia, and nausea management. The risk of hyperalgesia induced by remifentanil is counterbalanced by the administration of ketamine [16].

The possibility to use morphine as usual analgesia management 30 to 60 min before the end of surgery could be a bias, but the difference in clinical practice in each center should reduce this bias. In the same way, the possibility to perform preoperative regional analgesia could decrease the incidence of patients with ANI < 50 at the end of surgery but it is ethically inconceivable not to offer this type of analgesia whenever possible.

The scope of the trial and its conditions comply with daily practices. The investigators responsible for applying the protocol on each of the sites participating in the trial have clinical trial experience. The measures taken to establish the endpoints will be carried out by appropriately trained professionals on each site (anesthetist physician or resident, state-registered nurse anesthetist, clinical research associate). The study period is set at 2 years to ensure recruitment consistency among sites participating in the trial. Two patients are anticipated to be enrolled per site and per month to ensure the feasibility of this protocol.

Because of the paucity of well-conducted trials, the authors believe that a randomized-controlled trial will improve the evidence for using analgesia monitoring during general anesthesia and strengthen the current recommendations for intraoperative analgesia management.

## Trial status

Inclusions started in June 2019. Enrollment is ongoing. The last version of the protocol is 4.0. Inclusions are expected to be completed in August 2022.

## Abbreviations

ANI: Analgesia/Nociception Index
ASA score: American Society of Anesthesiologists Score
eCRF: Electronic case report form
ICU: Intensive care unit
MAC: Minimal alveolar concentration
NRS: Numerical Rating Scale
PACU: Post-anesthesia care unit
POMS: Postoperative morbidity survey
